## Abstract

**Background:**

Mass drug administration (MDA) and focal MDA (fMDA) using dihydroartemisinin plus piperaquine (DHAp), represent two strategies to maximize the use of existing information to achieve greater clearance of human infection and reduce the parasite reservoir, and provide longer chemoprophylactic protection against new infections. The primary aim of this study is to quantify the relative effectiveness of MDA and fMDA with DHAp against no mass treatment (standard of care) for reducing *Plasmodium falciparum* prevalence and incidence.

**Methods/design:**

The study will be conducted along Lake Kariba in Southern Province, Zambia; an area of low to moderate malaria transmission and high coverage of vector control. A community randomized controlled trial (CRCT) of 60 health facility catchment areas (HFCAs) will be used to evaluate the impact of two rounds of MDA and fMDA interventions, relative to a control of no mass treatment, stratified by high and low transmission. Community residents in MDA HFCAs will be treated with DHAp at the end of the dry season (round one: November to December 2014) and the beginning of the rainy season (round two: February to March 2015). Community residents in fMDA HFCAs will be tested during the same two rounds for malaria parasites with a rapid diagnostic test; all positive individuals and all individuals living in their household will be treated with DHAp. Primary outcomes include malaria parasite prevalence (n = 5,640 children aged one month to under five-years-old), as measured by pre- and post-surveys, and malaria parasite infection incidence (n = 2,250 person-years among individuals aged three months and older), as measured by a monthly longitudinal cohort. The study is powered to detect approximately a 50 % relative reduction in these outcomes between each intervention group versus the control.

**Discussion:**

Strengths of this trial include: a robust study design (CRCT); cross-sectional parasite surveys as well as a longitudinal cohort; and stratification of high and low transmission areas. Primary limitations include: statistical power to detect only a 50 % reduction in primary outcomes within high and low transmission strata; potential for contamination; and potential for misclassification of exposure.

**Trial registration:**

Identifier: Clinicaltrials.gov: NCT02329301. Registration date: 30 December 2014.

**Electronic supplementary material:**

The online version of this article (doi:10.1186/s13063-015-0862-3) contains supplementary material, which is available to authorized users.

## Background

The recent Zambian National Malaria Strategic Plan 2011 to 2016 calls for ambitious efforts to work towards malaria elimination, with the establishment of at least five malaria-free zones by 2015 [1]. The Zambian government, through its National Malaria Control Centre (NMCC), has successfully scaled up the main World Health Organization (WHO)-recommended malaria control interventions (for example, long-lasting insecticide-treated mosquito nets (LLINs), indoor residual spraying (IRS), and prompt effective treatment of malaria) over the past decade and is considering alternative strategies to further reduce malaria prevalence and burden [2]. While recognizing that eliminating malaria from the country may require many years to achieve, malaria elimination is a realistic milestone for Zambia in light of recent successes in reducing the malaria burden through a collaborative effort among the NMCC and its partners [2].

During the 2012 dry season (June to November) in Southern Zambia, the effectiveness of three large-scale malaria mass test and treatment (MTAT) intervention rounds were assessed with a community randomized controlled trial (CRCT) [3]. The MTAT intervention consisted of testing all individuals in intervention areas with rapid diagnostic tests (RDTs); all positive individuals were treated with artemether-lumefantrine (AL; MTAT-AL), which is the first-line drug for treating uncomplicated malaria in Zambia. The MTAT-AL intervention aimed to reduce community-wide malaria transmission by targeting persons infected with the asexual stage, and treating both asexual (blood) stage and immature sexual stage (immature gametocytes) infections of the *Plasmodium falciparum* parasite, thereby preventing onward transmission from infected individuals.

The results of the Zambia MTAT trial [3], as well as those from a recent trial of MTAT-AL in Burkina Faso [4] and Zanzibar [5], suggest that the use of MTAT-AL will likely be insufficient to achieve malaria elimination in many settings, for several important reasons. The generally short terminal elimination half-life of AL (less than three days), combined with the short duration of the treatment regimen (taken over three days), may provide little chemoprophylactic or chemo-suppressive protection against reinfection of *P. falciparum* [6]. Shifting to a longer lasting antimalarial therapy, such as dihydroartemisinin plus piperaquine (DHAp), will extend the chemo-prophylactic period and thereby help to extend the duration of transmission suppression during mass treatment interventions. DHAp has shown better efficacy compared to AL at clearing asexual blood stage malaria infections, but while DHA has a similarly short elimination half-life to AL, piperaquine has a significantly longer terminal elimination half-life of up to 63 days [7, 8].

The results from the previous MTAT trials also suggest that alternatives to the MTAT antimalarial delivery strategy are needed. One alternative strategy to avoid some important limitations of MTAT involves treating all individuals within a specified target area with an effective antimalarial, irrespective of having a parasite infection identified by an RDT, which would constitute community-wide mass drug administration (MDA) [9]. There are several potential advantages of using MDA, especially if coupled with DHAp (MDA-DHAp), over MTAT-AL. First, RDTs used for diagnosis in the previous MTAT strategy have been shown to miss up to 50 % of low-density malaria parasite infections [10], and thereby leave a substantial reservoir of infection in the community untreated, which may then sustain continued transmission. Such individuals with low-density parasite infections missed by RDTs under the MTAT will receive treatment under MDA. Second, because MDA-DHAp may also provide effective chemoprophylaxis against new infections for the entire target population (irrespective of RDT result), it is expected to provide a larger chemoprophylactic and chemo-suppressive effect to the community than limiting drug administration to only those individuals testing positive for a malaria infection by RDT [10, 11]. As a result, MDA-DHAp is potentially more effective and cost-effective than MTAT, due both to clearance of low-density infections and by prevention of new infections in the entire population [12].

An alternative to community-wide MDA is focal MDA (fMDA), which combines aspects of both MTAT and MDA. fMDA, in this trial, consists of testing all individuals in the community for parasites using RDTs and treating those that are positive. But in households where anyone had a positive RDT, all household members are treated with an effective antimalarial, such as DHAp (MDA-DHAp), irrespective of each person’s RDT result. As such, fMDA uses real-time information from RDT results to focus MDA activities to populations at greatest risk of having, as well and perhaps acquiring, an infection. Results of the 2012 MTAT-AL data analysis in this study site of Southern Province shows considerable clustering of *P. falciparum* infections identified by RDTs at the household level, suggesting that if one person tests positive, there is a higher chance (than random) that others in the house are also infected, potentially including those with low-density infections missed by RDTs. Such spatial clustering of infections in other settings has been well documented [13]. FMDA-DHAp may therefore provide a substantial advantage to MTAT-AL, in that it would clear more infections among individuals with parasite infections clustered in households, even among those with low-density infections missed by RDTs. Additionally, DHAp given to individuals in households using fMDA should provide sustained prophylactic protection for those individuals against new infections for up to two months, perhaps among those in the community most at risk of acquiring a new infection. At the same time, fMDA would limit drug exposure to those most at risk.

MDA and fMDA using DHAp represent two potential strategies to achieve greater clearance of human infection and reduction in the parasite reservoir, and both provide longer chemoprophylactic protection against new infections. The primary aim of this study is to quantify the relative effectiveness of MDA and fMDA with DHAp against no mass treatment for reducing *P. falciparum* parasite prevalence, confirmed out-patient malaria case incidence, and monthly infection incidence in areas stratified by high and low malaria transmission. It is hypothesized that two rounds of fMDA and MDA with DHAp will be significantly more effective than no mass treatment (standard of care) at reducing these health outcomes. A secondary objective of this study is to compare the cost and cost-effectiveness of the fMDA and MDA strategies with DHAp compared to no mass treatment.

Other outcomes related to the quality of program implementation will also be measured during this study to help understand why the MDA and fMDA with DHAp interventions were, or were not, found to be effective in this setting. These outcomes include: participant adherence of taking a full course of DHAp by the fMDA and MDA interventions; clearance of asexual stage parasites at day seven following the administration of DHAp; population coverage of the fMDA and MDA interventions in the study areas; and community acceptability of participating in the fMDA and MDA interventions. Measurement for these outcomes is summarized in the Methods/Design section below, with further details provided in the Additional file 1.

## Methods/design

### Study site

The study will be conducted in Southern Province Zambia in districts along Lake Kariba, including Gwembe, southern Kalomo, Siavonga, and Sinazongwe (Fig. 1). The population of this area was estimated at just over 330,000 living in roughly 56,000 households in 2011, based on a complete census of the study area conducted during the previous MTAT-AL trial, plus an updated census conducted for this trial in 2014. All households in the study area were enumerated using a geographic information system (GIS) prior to February 2014.

**Fig. 1 Fig1:**
[figure not shown]
Map of the study area, divided into 60 health facility catchment areas that serve as the unit of randomization

The area is primarily composed of the Tonga ethnic group. Livelihood typically consists of fishing and farming. While there are towns in the study area, the majority of the area is rural. The health system throughout the study area consists primarily of public sector health facilities, with health facility catchment areas (HFCAs) typically covering 500 to 1,500 households. All HFCAs were mapped and geographically defined prior to this study.

Malaria transmission in this area is low to moderate, with malaria parasite prevalence ranging from less than 1 % in some areas to more than 25 % in other areas. The high malaria transmission season in the study area follows the rainy season and lasts from January to May. Results from the 2012 MTAT-AL intervention identified two distinct areas of malaria transmission intensity, with higher transmission areas along the low-lying shores of Lake Kariba, and lower transmission areas inland from Lake Kariba.

There are current efforts to maintain high vector control coverage in the study area, with household coverage of LLINs estimated to be between 60 and 80 %. Additionally, a comprehensive IRS campaign to cover all households in the study area was conducted between November 2014 and January 2015, using the highly effective insecticide Actellic.

### Interventions

#### Dihydroartemisinin plus piperaquine

DHAp is the study drug used in this trial to treat *P. falciparum* parasite infections. DHAp was recently approved as the alternate first-line treatment in Zambia for uncomplicated malaria [14]. The DHAp used in this trial was manufactured by (Sigma Tau, Gaithersburg, Maryland, USA) and is branded as Eurartesim®. Eurartesim® is the only Stringent Regulatory Authority (SRA) approved DHAp product on the international market at this time.

All individuals meeting the inclusion and exclusion criteria to receive DHAp will be offered an age-appropriate course of the drug, according to the manufacturer’s recommendations and the national guidelines. DHAp dosing will be age-based (age-based dosing table provided in Additional file 1: Table S1). Based on the treatment guidelines for uncomplicated malaria set forth by the manufacturer and the WHO, a target dose of 4 mg/kg/day dihydroartemisinin and 18 mg/kg/day piperaquine for three days, with a therapeutic dose range between 2 and 10 mg/kg/day dihydroartemisinin and 16 and 26 mg/kg/day piperaquine, will be used (please see Additional file 1: Table S1 for the age-based dosing guidelines used for administering DHAp) [4].

#### Community-wide mass drug administration with dihydroartemisinin plus piperaquine

Under coordination with the Zambia NMCC, two rounds of MDA with DHAp are being implemented in December 2014 (end of dry season) and February 2015 (beginning of rainy season) in selected study site HFCAs. Spacing of the rounds was determined by the manufacturer recommendation of not receiving more than two courses of DHAp within two months [4]. Each round of the MDA-DHAp intervention consists of testing all individuals with an RDT, sharing the result of the RDT, and then offering an age-appropriate therapeutic dose of DHAp, irrespective of the RDT test result, among those consenting individuals meeting the inclusion criteria to receive DHAp, as outlined below and in Fig. 2. All consenting women in the MDA intervention not in the first trimester of pregnancy are offered DHAp.

**Fig. 2 Fig2:**
[figure not shown]
Participant flow chart to determine antimalarial treatment regimen under MDA-DHAp. Women of reproductive age (WRA): those 15 to 49-years-old; *RDT*: rapid diagnostic test; *HF*: health facility; *MDA*: mass drug administration; *DHAp*: dihydroartemisinin plus piperaquine

#### Household-level focal mass drug administration with dihydroartemisinin plus piperaquine

Under coordination with the Zambia NMCC, two rounds of fMDA with DHAp are being implemented in December 2014 (end of dry season) and February 2015 (beginning of rainy season) in selected study site HFCAs. Each round of the fMDA-DHAp intervention consists of testing all individuals with an RDT and then sharing the result of the RDT. An age-appropriate therapeutic dose of DHAp is offered to all consenting individuals meeting the inclusion criteria to receive DHAp, as outlined below and in Fig. 3. Among all other consenting eligible individuals in the household where a positive RDT result occurred among any member, an age-appropriate therapeutic dose of DHAp is offered, irrespective of the RDT test result of that individual. All consenting women in the fMDA intervention not in the first trimester of pregnancy are offered DHAp in accordance with the fMDA process just outlined.

**Fig. 3 Fig3:**
[figure not shown]
Participant flow chart to determine antimalarial treatment regimen under fMDA-DHAp. Women of reproductive age (WRA): those 15 to 49-years-old; *RDT*: rapid diagnostic test; *HF*: health facility; *MDA*: mass drug administration; *DHAp*: dihydroartemisinin plus piperaquine

#### Directly observed treatment of dihydroartemisinin and piperaquine in the focal mass drug administration and mass drug administration intervention rounds

A modified directly observed treatment (DOT) will be used to maximize adherence with the prescribed DHAp treatment among all individuals participating in the MDA intervention and all individuals in households with a member with a positive RDT in the fMDA intervention. At the community level, DHAP will be given by DOT on the first day of the household visit to all household members by the campaign team testing pairs. The second day of the treatment will not be given by DOT by campaign teams, but will be asked on the final day of treatment by an adherence monitoring officer working with the campaign teams. These adherence officers will make the second household visit to administer DOT for the third treatment dose, ask about adherence for the second dose, observe and count the treatment packets for the remaining pills, and provide additional instruction on full compliance if needed.

#### Inclusion and exclusion criteria of individuals participating in the intervention

Figures 2 and 3 present an overview of the MDA-DHAp and fMDA-DHAp inclusion and exclusion criteria. Children younger than three-months-old will be excluded from receiving DHAp, according to the manufacturer recommendations. Women in their first trimester of pregnancy will not be offered DHAp in the MDA or fMDA interventions. Instead these young children and pregnant women will be offered the appropriate dose of antimalarial treatment, according to the national treatment guidelines, if found to have a positive RDT.

Pregnancy status during the first trimester will be determined among women ages 12 to 49 years through direct questioning, and by offering a urine human chorionic gonadotropin rapid pregnancy test at the field visit for women unsure of their pregnancy status or reporting longer than five weeks since last menstruation. All consenting women in the MDA and fMDA interventions with a negative RDT deemed to be in the first trimester of pregnancy will receive no malaria treatment. All consenting women deemed to be in their first trimester of pregnancy with a positive RDT will receive the recommended standard of care treatment for uncomplicated malaria in Zambia among women in their first trimester of pregnancy, which consists of age-appropriate treatment with oral quinine for seven days.

All individuals with suspected severe malaria or other severe illness (including symptoms of severe anemia, prostration, impaired consciousness, respiratory distress, convulsions, circulatory collapse, abnormal bleeding, jaundice, and passing black or brown (dark) urine) will be referred to the nearest health facility for treatment, and will not be included in the MDA or fMDA interventions or associated research.

#### Community mobilization

MDA requires high levels of participation and adherence to the full treatment course to be as effective as possible. To encourage participation, several activities were conducted in advance of and during the treatment campaigns in order to broaden and strengthen community awareness. First, information about the campaigns, the treatments, and the process were shared through the Ministry of Health and Ministry of Community Development, Mother and Child Health structures, including among community health workers to begin discussions at local levels. Second, community sensitization meetings were held throughout campaign areas across nine districts to inform leaders at the district level, including district councilors, religious leaders, and lead educators, and at the chiefdom level, with special outreach to chiefs, village headmen, local community health workers, and community members gathered for village entry meetings. Information, education, and communication materials were developed with the Zambia NMCC on malaria and pretested in campaign areas, containing behavior change communication messages for community members and community leaders. These were translated into the local language and distributed at these community sensitization meetings. Third, radio spots were developed and aired in the local language in target areas, along with a series of radio group episodes in which community members engaged with campaign health experts to learn about the program and discuss the benefits of participation.

### Standard of care and control group

Standard of care in Zambia, including the study area in Southern Province, consists of identification of malaria infections and clinical cases through passive case detection at local health facilities or community health workers. Zambian national policy stipulates that individuals seeking care for a fever be given a malaria diagnostic test by RDT or microscopy. Individuals with confirmed malaria are then treated with the first-line antimalarial in Zambia, which is AL. When no diagnostic test is available at a health facility, a clinical diagnosis is made based on signs and symptoms, and treatment follows the identical protocol as with RDT-confirmed malaria cases. Standard of care does not include any kind of active surveillance for malaria parasite infection or mass treatment of the population with antimalarials.

### Study design

A CRCT will be used to evaluate the impact of two rounds of the MDA-DHAp or fMDA-DHAp (the two intervention arms) at reducing malaria parasite infection prevalence and incidence, as well as malaria-related morbidity, compared to a control group receiving standard of care. Communities, or clusters, are defined by HFCAs and serve the unit of randomization. A total of 60 health facilities and their catchment areas are included in the study.

#### Stratification

As the impact of the MDA and fMDA interventions are expected to vary across malaria transmission strata, the 60 HFCAs included in the study have been stratified into high and low transmission strata. To do this, parasite prevalence in each HFCA was estimated with a kriged continuous surface of parasite prevalence from data from the baseline 2014 parasite survey. Catchments were then ranked from highest to lowest parasite prevalence. The top 30 HFCAs were included in the high transmission strata, while the bottom 30 were included in the low transmission strata; the resulting cut point between the high and low transmission strata was approximately 10 % parasite infection prevalence.

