### Randomization sequence generation and allocation concealment

Pre-existing maps of HFCAs were used to classify households as belonging to a specific HFCA, which serve as the unit of randomization. To ensure balance across large and small HFCAs, which could potentially affect the quality of program implementation and other related unobserved confounding factors, HFCAs were characterized as having either a large or small population catchment size. This classification was based on a cut-point obtained from the mean population catchment size across the 60 HFCAs. Within the high and low transmission strata and the large and small population catchment size classifications, the random allocation rule will be used to assign HFCAs to the fMDA-DHAp, MDA-DHAp, or control group. As a result of this process and the stratification outlined above, the 60 total HFCAs are split into 10 HFCAs per treatment group (MDA, fMDA, and control) in the high transmission strata (n = 30 HFCAs), and 10 HFCAs per treatment group (MDA, fMDA, and control) in the low transmission strata (n = 30 HFCAs).

After allocation, the appropriate intervention will be implemented in the entire catchment area according to treatment group assignment. Allocation of study arms will not be blinded to the deliverers of the intervention or to the main investigators, as delivery of the intervention precludes the possibility of allocation concealment. However, data collectors in the follow-up parasite prevalence survey, as outlined below, will be blinded to allocation. All primary analyses will also be blinded to analysts by the use of concealed code for the study arm variables in the final dataset.

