#### Baseline and follow-up household parasite surveys

##### High transmission strata

The coefficient of variation (CV) was estimated using data from a previous study of the 2012 MTAT-AL in the study area (CV = 0.31). Based on the number of clusters available in the high transmission strata (n = 10 in each of the three treatment groups, total of 30 clusters), a statistical power of 80 %, a probability of committing a type two error of 5 % (one-tailed test), and simple random sampling used to obtain the sample of children in each household survey, a sample size of 39 children under-years-old per HFCA per treatment group will be needed to detect 12 % absolute detectable difference in parasite prevalence between any two groups, from a baseline of 30 % (a 40 % relative difference, going from 30 to 18 % parasite prevalence). This detectable difference equates to a crude odds ratio of 0.51. With survey non-response assumed to be 20 %, a sample size of 470 children per treatment group (47 children per cluster), totaling 1,410 children under six-years-old per survey round will be sought (Additional file 1: Table S2). This sample size equates to a sample size of 1,410 households sampled per survey round.

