### Statistical analysis plan

The primary analysis for estimating the treatment effect between MDA, fMDA, and control HFCAs for primary outcome one (parasite prevalence) and two (parasite infection incidence rates) will be based on intention to treat at the individual level for infections measured by RDT and PCR. The analysis of parasite prevalence will use a logistic or log binomial model, while the analysis for infection incidence will use a Poisson or negative binomial model. Models will include a random intercept at the HFCA level (randomization unit), fixed effect for intervention exposure, time period (pre- and post-intervention), plus other potential confounding factors. Standard errors will be estimated, with the addition of repeated measures among individuals.

Data for total and confirmed OPD and IPD malaria case incidence (outcome three) among all ages will be analyzed on an intention-to-treat basis. Routine data on case counts will be analyzed using a Poisson or negative binomial model, with random intercepts at the HFCA level. The models will include a fixed effect for study arm and time period (pre- and post-intervention), plus other potential confounding factors.

Differences in prevalence measures (RDT positivity) at each round will be assessed using an *X*^2^ test, as well as logistic regression models to account for potential confounding factors, on an intention-to-treat basis. Logistic models will include a random intercept for HFCA, as well as fixed effects for other potential confounding factors. Trends in parasite prevalence across rounds, with the inclusion of the control group, will then allow rapid assessment of the effect of the fMDA and MDA interventions over time, after removing the seasonality effect.

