The strengths of this trial include the fact that a rigorous study design (a CRCT) will be used to assess the impact of the MDA and fMDA interventions, as compared to a control of no mass treatment (standard of care). The study is also powered to assess differences between each treatment group (MDA and fMDA) and the control group, within areas of high and low transmission, with 80 % statistical power. The study uses robust measures of malaria parasite infection at the point of contact using RDTs, as well as PCR, for detecting low-density parasite infections, as part of the parasite surveys and the longitudinal cohort. The study also uses multiple methods for measuring malaria-related outcomes, including malaria parasite infection prevalence ascertained from a pre- and post-parasite survey, malaria parasite infection incidence using a longitudinal cohort of individuals selected randomly from within each HFCA, and confirmed malaria case incidence throughout the study using routine health management information system (HMIS) data in the study area. Buffer areas between contiguous HFCAs with different interventions are being used to limit contamination and misclassification bias. Measures of the quality of the implementation of the MDA and fMDA interventions will be obtained to help with the interpretation of results; these include MDA and fMDA population coverage, adherence to DHAp, parasite clearance after DHAp, community perceptions and acceptability of the MDA and fMDA interventions, and multiple measures of operational coverage. Lastly, a rigorous analysis plan will be followed, for assessing the impact of each intervention compared to a control group, while accounting for potential contextual and confounding factors within random-effect regression models.

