Noted weaknesses of this trial include a less than ideal number of community randomization units (N = 60), especially when stratified by high (n = 30) and low (n = 30) transmission strata. The sample size within the high and low transmission strata will only allow the detection of approximately a 50 % reduction in parasite prevalence and infection incidence between intervention groups, with 80 % statistical power; the threat of a type two error is therefore higher than ideal. The primary analysis will be based on the intention-to-treat principle; there is potential for misclassification of exposure using this approach. Secondary analysis using a per-protocol approach will be used mitigate any misclassification of exposure. And lastly, there is always the potential for error in the measurement of outcomes, exposure to the interventions, and potential confounding factors in such a large and complex trial. We have gone to considerable length to try and minimize such error through the use of electronic data capture systems in the field and robust diagnostic methods.

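### Effects are sought and sized by transmission stratum, but the listed model has no stratum or arm-by-stratum term, so it neither yields nor compares the stratum effects

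*Protocol article*

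**What the plan says.** **Aim and design.** The Background sets the aim in areas split by high and low transmission, and the opening of the Discussion repeats it. The Stratification section gives the reason: "As the impact of the MDA and fMDA interventions are expected to vary across malaria transmission strata". Randomisation then places "10 HFCAs per treatment group (MDA, fMDA, and control) in the high transmission strata", and the same number in the low stratum, so each arm has 20 HFCAs overall.

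**Sizing.** Under Sample size and statistical power, the parasite survey, the cohort and RDT positivity are each sized separately by stratum, arm against control. The strengths paragraph of the Discussion claims power for these comparisons "within areas of high and low transmission, with 80 % statistical power". The weaknesses paragraph concedes: "The sample size within the high and low transmission strata will only allow the detection of approximately a 50 % reduction in parasite prevalence". No detectable effect is given for the two strata together.

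**Analysis.** For prevalence and incidence, the Statistical analysis plan section states: "Models will include a random intercept at the HFCA level (randomization unit), fixed effect for intervention exposure, time period (pre- and post-intervention"), plus other potential confounders. It names neither stratum nor an arm-by-stratum term, and does not say that the strata are modelled separately. In the same section, the primary cost-effectiveness ratios are unstratified and the stratified ones secondary.

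**The concern.** The aim, the design and the sizing all point to two stratum-specific effects per intervention, while the listed model points to one effect across all HFCAs. The article therefore leaves two things open: which of these is the primary effect, and how a difference between strata would be judged.

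This matters because the result is meant to guide the national programme. If the only stratum-level evidence is whether each comparison reaches significance, a difference in significance can be taken for a difference in effect. The survey is especially exposed. On the plan's own figures, it can detect a 40% reduction in the high stratum but only a 60% reduction in the low one, so the same true effect has quite different power in the two.

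**Working it through.** **Inputs (Sample size and statistical power).** There are 10 HFCAs per arm per stratum, with "a statistical power of 80" %. The error rate is worded as "a probability of committing a type two error of 5 % (one-tailed test"); I read the 5% as the one-sided significance level, and the reproduction below supports that.
- Survey: 39 children per HFCA in each stratum. High stratum 30% to 18%, from "2012 MTAT-AL in the study area (CV = 0.31"). Low stratum 10% to 4%, CV 0.41.
- Cohort: CV 0.50 in both strata. High stratum 25 persons per HFCA, 1.8 to 0.91 infections per person-year. Low stratum 27 persons, 0.6 to 0.28.

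**Formula (Hayes and Moulton, unmatched, c = 10).**

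z = √[(c − 1)(p0 − p1)² / V], power = Φ(z − 1.645)

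- Survey: V = [p0(1 − p0) + p1(1 − p1)]/m + k²(p0² + p1²)
- Cohort: V = (r0 + r1)/y + k²(r0² + r1²), with rates r in place of p

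**Step 1: reproduce the plan's 80%.**
- Survey, high: V = 0.00917 + 0.01176; z = √(9 × 0.0144/0.02093) = 2.488; power 80%.
- Survey, low: V = 0.00329 + 0.00195; z = √(9 × 0.0036/0.00524) = 2.486; power 80%.
- Cohort, high: V = 0.1084 + 1.0170; z = √(9 × 0.7921/1.1254) = 2.517; power 81%.
- Cohort, low: V = 0.0326 + 0.1096; z = √(9 × 0.1024/0.1422) = 2.546; power 82%.

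The survey figures match and the cohort figures are within 2 points.

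**Step 2: same true relative reduction in both strata.** The shared effect is my assumption, shown over a range. With independent strata:
- P(exactly one significant) = pH(1 − pL) + pL(1 − pH)
- P(neither significant) = (1 − pH)(1 − pL)

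| Outcome | Shared reduction | Power high | Power low | Exactly one | Neither |
|---|---|---|---|---|---|
| Survey | 60% | 99% | 80% | 21% | <1% |
| Survey | 50% | 94% | 64% | 38% | 2% |
| Survey | 40% | 80% | 46% | 52% | 11% |
| Cohort | 50% | 82% | 76% | 33% | 4% |
| Cohort | 40% | 62% | 57% | 48% | 16% |

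A check on the log-ratio scale gives 37% and 52% for the survey at 50% and 40%, and 27% and 47% for the cohort. For reference, two independent tests with exactly 80% power disagree in 2 × 0.8 × 0.2 = 32% of trials.

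**Step 3: both strata combined.** With pooled z = √(zH² + zL²), 80% power needs z = 1.645 + 0.842 = 2.486. The survey reaches this at about a 35% reduction and the cohort at about 38%, against 40% and 60% (survey) and 49% and 53% (cohort) within strata. For a shared 40% reduction:
- Survey: z = √(2.488² + 1.544²) = 2.928, power 90%.
- Cohort: z = √(1.958² + 1.812²) = 2.668, power 85%.

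**Step 4: precision of the interaction.** On the log-ratio scale, the variance is [(1 − p0)/(m·p0) + (1 − p1)/(m·p1) + 2k²]/9. At the plan's own contrast, the standard errors are 0.202 (high, ratio 0.60) and 0.362 (low, ratio 0.40). The difference has standard error √(0.202² + 0.362²) = 0.415. The true difference is ln(0.60/0.40) = 0.405, so the expected z is 0.98 and two-sided 5% power is about 16%.

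**The case against.** The strongest objection is that the analysis section is a short sketch in a condensed article, and that interaction terms and rules for reading subgroups usually sit in a full analysis plan, which is not shown. That plan may settle the matter. But the article does list its model terms, and the list does not match the aim and sizing stated in the same document.

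A reader might infer more than the text supports:
- *That the plan has no pooled estimate and wastes power.* Read literally, the listed model spans all MDA, fMDA and control HFCAs, which is a pooled effect, and the primary cost-effectiveness ratios are unstratified too. What is missing is a declaration that this effect is primary, and its sizing.
- *That the plan will claim effect differences from separate p-values.* No section commits to this. The stated hypothesis is each arm against no mass treatment; reading by stratum is suggested only by the aim and the sizing.
- *That disagreement between strata is the likeliest outcome of equal effects.* It is common, but among the 40 to 50% scenarios it exceeds half only for the survey at 40%. The unequal-power argument is also mainly about the survey, since the cohort strata are similar.
- *That moderate effects would be missed in both strata.* At a shared 40% reduction this happens in only 11% (survey) and 16% (cohort) of trials.

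Two further objections stand. The figures come from a two-group, post-intervention formula, whereas the planned models also use the baseline period and covariates. And whether the pooled or the stratum-specific effect comes first is a choice of estimand, not a matter of right or wrong. The within-stratum power limit is openly disclosed as one of several weaknesses.

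**Conclusion.** The concern holds as a mismatch inside the article. Effects are wanted by stratum and sized by stratum, but the listed model carries a single exposure effect and cannot deliver or compare stratum effects. Whether the primary effect is pooled or within stratum is unsettled.

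The size depends on how results are read. If they are read stratum by stratum, equal 40 to 50% reductions would give significance in exactly one stratum in roughly a third to a half of trials. That rests on an assumed shared effect, independence of the strata, the plan's CVs and baseline levels, and one-sided 5%. It does not establish that the trial will be misread. The correction is worth making because it is nearly free.

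**What to change.** In the Statistical analysis plan section, for each arm against control:
1. Fit one model on all 60 HFCAs with a stratum term and an arm-by-stratum term, the latter attached to whichever term carries the intervention effect.
2. Report both stratum-specific effects, the interaction with its confidence interval, and the stratum-adjusted pooled effect.
3. Declare whether the pooled or the stratum-specific effects are primary. That choice is the sponsor's.
4. State that any claim that the effect differs by transmission level rests on the interaction, not on significance in one stratum only.

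In the weaknesses paragraph of the Discussion, add the pooled detectable reductions: about 35% (survey) and 38% (cohort) on the plan's assumptions.

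**Cost.** Wording and two model terms; no new data. The interaction will be openly imprecise, with about 16% power for the plan's own 40% versus 60% contrast in the survey. Its use is to stop differing p-values being read as differing effects, not to prove a difference. The pooled effect averages two settings and should be labelled so.
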